##### Patient non-inclusion criteria

Patients consulting for reasons other than sexual, urogenital or psychological will not be included. Patients consulting for one of the required reasons but who are unable to speak French, patients with psychiatric disorders affecting judgement and patients unable to sign an informed consent form were excluded.

##### GP inclusion criteria

The volunteer GPs are involved in the Department of Primary Care as trainers. GPs and patients from these offices are representative of the French population consulting in primary care [23].

##### GP non-inclusion criteria

GPs with an exclusive specialty (e.g., acupuncture, homeopathy) and physicians who have received specialised training in sexology and in communication skills during specific training or dedicated tuition will not be included in the sample of GPs.

#### Intervention

##### Intervention

The intervention will consist of a training session with the aim of directing the GPs to use the strategies found during the qualitative part of the pilot study. At an interactive 4-h workshop, GPs assigned to the IG will be trained to handle cases. The session will begin with a brainstorming session to bring out the GPs’ knowledge of PE and any questions that they have on the subject. This will be followed by a presentation which will describe PE, its different types and definitions, the physiopathology and aetiology of PE, and the treatments available [8]. These theoretical elements will be presented through a slide presentation, designed and approved by all the committee members. The chosen definition includes the three criteria of the ISSM (time, loss of control, and negative personal consequences) without mentioning in detail the ‘1-minute’ factor [6]. The results of the qualitative phase will be explained and the different strategies will be explicitly defined to provide operational and usable approaches to communication [22]. The six strategies were divided into two sections:

three attitude-related strategies for revealing the problem:Being particularly receptive to the patient throughout the consultation: especially at the end when the physician was about to open the door, in order to create a gap that the patient could use to express his problem. The physician consciously creates an attentive environment, using non-verbal behaviour which will encourage the patient to speak freelyUsing humour: lightening the atmosphere by using gentle humour without being vulgar or insensitiveTaking a matter-of-fact approach to play down any embarrassment in the patient’s view of sexuality: emphasising the natural and mechanical function of sexuality allows the GP to play down the emotional aspect of the subjectThree investigative strategies with interviews deliberately directed towards sexual dysfunction:Systematic questioning during consultations dedicated to preventionSymptoms that the patient could be experiencing: the GP suggests a list of signs and symptoms connected to the current clinical situation, for instance: ‘you’re presenting symptoms of depression, and depression may bring on physical, psychological, and even sexual tiredness’. The patient chooses one of these to talk about his PEFacilitating the patient’s verbal expression, enquiring about the patient’s psycho-social and medical history and his daily environment enables the subject of PE to be raised

The training session will be provided by the Steering Committee member in each of the four regions. Their expertise is as follows: three have had specialised training in sexology and three have had specialised training in education. They will receive audio-visual training in the presentation of the slides to ensure the replication of the intervention. GPs will be trained, with practice situations, using role-play performed with the committee member and the other GPs. Available treatments, based on the ‘guidelines for the diagnosis and treatment of premature ejaculation’ [8] will be presented during the session. The session will end with the presentation of the outcome questionnaires.

The intervention session will follow this agenda:30 min will be devoted to brainstorming1 h to the presentation of theoretical elements, and2 h will be devoted to role-play practice situations

The intervention will occur at the GP’s surgery or during a professional meeting, depending on the choice of the GP.

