## Background

Many male patients complain about their problems with ejaculation: 21–30% of men, aged between 18 and 80, have admitted suffering from a decrease in, or loss of control of, their ejaculation [1–3]. The quality of life of the patients and their partners is impaired compared with men not suffering from premature ejaculation (PE) [4]. In addition, anorgasmia and low libido, as well as depression and anxiety, are comorbidities significantly associated with PE [5]. Defining PE is not simple: seven to ten different definitions have been proposed since 1970 [6, 7]. The definition chosen by the International Society for Sexual Medicine (ISSM) [8, 9] was an ejaculation which always, or nearly always, occurred prior to, or within about 1 min of, vaginal penetration; the inability to delay ejaculation during all or most vaginal penetrations, and negative personal consequences, such as distress, anxiety, frustration and/or the avoidance of sexual intimacy. Apart from the distinction between acquired and lifelong PE, two other categories have been described: natural variable PE and premature-like ejaculatory dysfunction [10]. Natural variable PE corresponds to the normal variation in sexual performance. The premature-like ejaculatory dysfunction corresponds to the patient’s distorted perception of time before ejaculation: the patient is convinced that he is suffering from PE although his Intravaginal Ejaculation Latency Time (IELT) is more than 1 min. While the prevalence, according to men’s self-reports, is 30%, the rate drops to 3% when the time factor is considered in isolation [5]. This statement illustrates the incompatibility between the academic definition and the actual complaints from patients.

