## Methods

### Outcome

The primary outcome is the incidence of patients bringing up the topic of PE with their GP.. This was undertaken in the group where the GPs received training in communication skills directed towards this pathology, compared with the patients who received the usual care procedures.

The secondary outcome relates to the variation in the quality of life of patients after they have addressed the topic of PE as measured by the SF-12 questionnaire.

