##### Usual care

GPs registered in the CG will provide care according to their usual practices. The definition of usual care described here is ‘the clinical care without any value judgment’ and centred on the patient [24]. We concentrated on reducing influences on the control GPs in the information session and through the GP questionnaire [25]. The GPs in the CG will attend a 2-h information session to learn about the case report forms and the patients’ inclusion/exclusion criteria. The session will be provided by the Steering Committee member in each of the four regions. A slide presentation, designed and approved by all the committee members, will be presented along with the reasons for the consultation and the GP questionnaire to be completed.

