#### Statistical methods

Analyses will be performed using Stata software, version 13 (StataCorp, College Station, TX, USA). All data will be analysed on intention to treat. The tests will be two-sided, with a type I error set at *α* = 0.05. Baseline characteristics (GPs and their patients) will be presented for each randomisation group as the mean ± standard deviation (SD) or the median (interquartile range) according to statistical distribution for continuous data and according to the number of patients and associated percentages for categorical parameters.

The comparisons between the randomised groups will be carried out using the Student *t* test or the Mann-Whitney test where appropriate, (1) normality verified by the Shapiro-Wilk test and (2) homoscedasticity by the Fisher-Snedecor test for quantitative parameters and using chi-squared or Fisher’s exact tests for categorical variables.

Outcomes will pertain to the cluster level using usual statistical tests and with more specific approaches at the individual level. Hierarchical regression models (generalised linear mixed model due to binary endpoint) will be performed as primary analysis: (1) to estimate the effect of intervention on the incidence of new cases of patients suffering from acquired and lifelong PE, natural variable PE and premature-like ejaculatory dysfunction and (2) to take into account the variability between and within, the GP cluster groups. Intra-class correlation coefficients will be presented by arm with a 95% CI. Then, GP characteristics (gender, age, geographical area) or patient characteristics (age, socioeconomic status) should be considered as covariate (fixed effects in mixed models) in adjusted multivariable analyses. The adjusted and unadjusted results will be presented: absolute numbers of patients who have raised the topic of PE with their related GP, relative risks and 95% CIs.

For secondary endpoints, comparisons at the individual level between randomised groups will be performed using an analysis of covariance for correlated data with the baseline score as a covariate, as suggested by Klar and Darlington [31] for the SF-12 quality of life scores. Results will be expressed as effect-sizes and 95% CIs. The PEDT will be analysed as a quantitative score using statistical methods described for the SF-12 quality of life and as a binary outcome (< ≥ 11) with the use of a generalised linear mixed model.

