## Discussion

This intervention study will be the first concerned with PE in the area of primary health care. Six different strategies for tackling the subject were brought to light after a qualitative phase with GPs was compared with usual care procedures in primary health care. A French version of the Premature Ejaculation Diagnostic Tool will be used to detect patients from the IG and the CG who suffer from PE.

One major limitation is the unblinded GPs in the IG. As the intervention is based on training in strategies to tackle PE, it was impossible to leave them blind to the main aim of the study. The evaluation of the diagnosis of PE will be made by the GP. This limitation is counterbalanced by the fact that the PEDT sent after 1 month will also contribute to making the positive or negative diagnosis of PE.

We selected our participants via an e-mail, mentioning a study on ‘sexual dysfunction’ at the first step of the study. We wanted to inform them about the topic raised during the intervention. The GPs in the CG knew that the study was investigating sexual dysfunction: this could lead to increased awareness of sexual dysfunction, including PE, and thereby lead to an increase in the rate of consultations where PE was raised. We did not mention ‘sexual dysfunction’ on any other occasion to the CG.

The definition of PE references a pathology concerned with ‘vaginal penetration’. However, we want to enlarge the study to include men with a different sexual orientation. We did not include any questions about heterosexual or homosexual orientation in our questionnaires.

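### Only intervention GPs are taught a working definition of PE, and GP-identified cases are used interchangeably with topic raised, so the primary outcome may be classified differently by arm

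*Protocol article*

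**What the plan says.** All references are to the protocol article.

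- **Intervention.** The workshop includes "a presentation which will describe PE, its different types and definitions". On the working definition it says: "The chosen definition includes the three criteria of the ISSM (time, loss of control, and negative personal consequences) without mentioning in detail the" one-minute factor.
- **Usual care.** Control GPs "will attend a 2-h information session to learn about the case report forms" and the eligibility criteria. Their slides also cover the reasons for consultation and the GP questionnaire. No definition of PE is listed. The section adds that the team tried to limit influence on control GPs, both in the session and through the questionnaire.
- **Discussion.** After the recruitment e-mail, sexual dysfunction was not mentioned "on any other occasion to the CG". On assessment: "The evaluation of the diagnosis of PE will be made by the GP". The next sentence offers the 4-week PEDT as a counterbalance.
- **Outcome.** "The primary outcome is the incidence of patients bringing up the topic of PE with their GP".
- **Statistical methods.** The primary mixed model is meant "to estimate the effect of intervention on the incidence of new cases of patients suffering from acquired and lifelong PE, natural variable PE"; the list of case types also names premature-like ejaculatory dysfunction. The results to be reported, however, are numbers of patients who raised the topic.
- **Outcomes and measurements.** The final diagnosis of PE refers to the patient-completed PEDT.

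**The concern.** Whoever decides that a consultation counts as an event needs the same rule in both arms. Here one arm is taught what PE is and which types exist, and the other, as far as the article describes, is not. If the GP's label decides the event, a man who mentions poor ejaculatory control may be counted by a taught definition in one arm and by the GP's own idea of PE in the other.

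This differs from the lack of blinding that the Discussion concedes. It would remain with fully honest GPs, because the training itself may change what they regard as PE. At stake is whether a difference between arms shows that more men spoke about the problem, or partly that the same talk was labelled differently.

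**Working it through.** **Step 1. Does the GP's label enter the primary outcome?** The article gives the same pilot figures under two descriptions.

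| Section | How the figures are described |
|---|---|
| Feasibility | Patients identified as suffering from PE: 8/26 = 30.8% (intervention), 4/61 = 6.6% (control) |
| Abstract | 6.6% and 30.8% are rates of consultations in which the topic was raised |
| Sample size estimation | 6.6% is the incidence of control patients who brought up PE |
| Statistical methods | The model is for new cases; the reported results are patients who raised the topic |

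A case identified by the GP and a topic raised by the patient are treated as one event, so a labelling difference can reach the primary outcome.

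**Step 2. Does the PEDT remove the problem?** It is a patient self-report, the same in both arms, so a diagnosis based on it does not depend on the GP's definition. It is returned 4 weeks later and asks about the patient's condition. It cannot show what was said in the consultation, so it does not protect the outcome in the Outcome section.

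**Step 3. How large could the effect be?** The plan gives no figure for this, so none can be reproduced. What follows is an illustration.

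Inputs from the article: 300 patients per arm, 15 per GP, ICC 0.05 to 0.20, two-sided alpha 0.05. Assumptions of mine: the same true share c of men voices an ejaculation complaint in both arms, intervention GPs count all of them, and control GPs count a share s.

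- Observed relative risk with no true effect: c/(c × s) = 1/s.
- Effective n per arm: 300/(1 + 14 × ICC), which is 300/3.8 = 78.9 at ICC 0.20 and 300/1.7 = 176.5 at ICC 0.05.
- Chance of a significant result favouring the intervention, with d the difference in observed rates, p̄ their mean and n the effective size: Φ{[d − 1.96 √(2p̄(1 − p̄)/n)] / √([p1(1 − p1) + p2(1 − p2)]/n)}.

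For c = 10% and s = 0.5 (10% v 5%) at ICC 0.20: √(0.13875/78.9) = 0.0419, times 1.96 = 0.0822. Then (0.05 − 0.0822)/√(0.1375/78.9) = −0.0322/0.0417 = −0.77, and Φ(−0.77) = 0.22. At ICC 0.05 the same steps give 0.43.

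| s | False RR | c = 10%: ICC 0.05 / 0.20 | c = 20%: ICC 0.05 / 0.20 |
|---|---|---|---|
| 0.9 | 1.11 | 5% / 4% | 7% / 5% |
| 0.75 | 1.33 | 13% / 8% | 23% / 13% |
| 0.5 | 2.0 | 43% / 22% | 75% / 42% |
| 0.25 | 4.0 | 83% / 50% | 99% / 82% |

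With no labelling difference the chance in this direction is 2.5%. A small difference hardly matters; a large one does. If intervention GPs were the stricter group, the ratio would fall below 1 and a true effect would be understated.

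**The case against.** The strongest reply has four parts.

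1. **The GP questionnaire is not shown.** The article is condensed, and both arms are taken through their forms. A common event rule printed there cannot be excluded. This stands, and the point must be conditional on it. It does not remove the asymmetry in teaching or the interchangeable use of two events, both of which are in the text.

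2. **The PEDT is a stated counterbalance, and raising a topic needs less judgement than making a diagnosis.** Both are true. The first protects only a PEDT-based diagnosis. The second would limit the bias if topic raised were consistently the event, but the model is written for cases.

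3. **The direction is not shown.** A reader might infer that the training must inflate the intervention arm, since the model counts premature-like dysfunction, which the Background describes as a latency above one minute, and a GP who thinks in terms of time could leave such men out. The article does not establish this. The taught definition keeps all three ISSM criteria and could make trained GPs stricter than colleagues who count any complaint. Nothing says what control GPs use.

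4. **The Background's prevalence contrast is no measure of s.** It says that prevalence by self-report "is 30%, the rate drops to 3% when the time factor is considered in isolation". A reader might take this as a bound of 0.1 on the share that control GPs would count. It compares population prevalences under two criteria, not GPs labelling the same conversation, so it shows only that definition matters.

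The article also has a stated reason for telling control GPs little: awareness could raise the control rate. That argues against teaching them a definition, but not against a shared recording item.

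**Conclusion.** The point holds as a risk of differential classification of the primary outcome. Definition teaching is described for one arm only, the GP evaluates the diagnosis, and GP-identified PE is used interchangeably with topic raised. The PEDT does not cover the outcome that is named as primary.

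The documents do not support the statement that part of any observed increase is reclassification. Inflation in favour of the intervention is plausible, but direction and size are unknown. The illustrative figures (false relative risk 2, and a 22% to 43% chance of significance at c = 10%, s = 0.5) rest on assumed values of c and s, full counting by intervention GPs, and 300 patients analysed per arm. At s = 0.9 the inflation is slight. At s = 0.25 the false ratio of 4 equals the planned ratio of 20% to 5%, but with c = 10% the rates would be 10% v 2.5%, so the planned contrast itself is not reproduced.

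**What to change.** Score the primary outcome in both arms only from one identical, neutrally worded item on the GP form: whether an ejaculation complaint was spoken about in the consultation, regardless of whether the GP considers it PE. Record the GP's diagnosis as a separate item, keep it and the PEDT as separate outcomes, and rewrite the primary model in Statistical methods for the spoken-about item. If the shared form already has such an item, say so and name it as the source of the primary outcome.

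Do not add PE teaching to the control session. Place the item among other consultation topics so that control GPs are not primed.

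The cost is at most one form item and a few sentences of text. The downside is some residual cueing of control GPs by the item. The article says recruitment was not complete at submission, so the sponsor should also state how any patients recorded before the change will be scored.

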##### Usual care

GPs registered in the CG will provide care according to their usual practices. The definition of usual care described here is ‘the clinical care without any value judgment’ and centred on the patient [24]. We concentrated on reducing influences on the control GPs in the information session and through the GP questionnaire [25]. The GPs in the CG will attend a 2-h information session to learn about the case report forms and the patients’ inclusion/exclusion criteria. The session will be provided by the Steering Committee member in each of the four regions. A slide presentation, designed and approved by all the committee members, will be presented along with the reasons for the consultation and the GP questionnaire to be completed.

#### Data collection

##### Outcomes and measurements

To measure the incidence of patients suffering from acquired and lifelong PE, natural variable PE and premature-like ejaculatory dysfunction, the final diagnosis of PE will be made by referring to the answers given to the Premature Ejaculation Diagnostic Tool (PEDT) sent back by the patient 4 weeks after the consultation (please refer to the ‘Measurements’ section). The patients suffering from PE will be identified if their score is higher than 9 on the PEDT. The PEDT questionnaire is an extensively validated, self-report measure that can systematically assess DSM-IV-TR criteria to provide accurate diagnoses of PE/no-PE [26]. It is a screening tool with cut-off scores, brief and easy to administer, and recommended by the International Society of Sexual Medicine [8, 26, 27]. The self-report questionnaire, in our opinion, seems to handle delicate, intimate questions with appropriate sensitivity. We followed a linguistic and cultural validation procedure to obtain a French version of the questionnaire. Additional file 4 is an abstract describing the procedure we followed.

Patients in the two groups will have to complete a self-report questionnaire on quality of life, the SF-12 questionnaire, in a French-validated version right after the consultation, and again, 4 weeks after the consultation [28]. The SF-12 questionnaire right after the consultation will be available in the waiting room. The SF-12 questionnaire, 4 weeks after the consultation, will be posted or e-mailed to the patient. The SF-12 is a self-report questionnaire exploring quality of life [28]. The original questionnaire contained 36 items divided into eight scales, the SF-36 [28]. The SF-12 was created to shorten the responses and included one or two items from each of the eight SF-36 scales. The French version of the SF-12 is correlated to the SF-36 [28]. We chose a general quality of life self-report questionnaire for several reasons. A generic scale was useful to avoid influencing patients in the CG. The availability of a validated French version was another argument supporting the choice of this scale [28].

### Feasibility

As far as we are aware, this interventional multicentre study will be the first one concerned with PE in the area of primary health care. We created a pilot intervention study in primary care in order to estimate the feasibility of such a study design, as well as the incidence of diagnosed PE with, and without, the use of strategies. Thirteen GPs agreed to participate in the IG, six of whom included their patients in the study. Twenty-four GPs participated in the CG, 13 of whom included their patients in the study. The GPs in the IG included 26 of their patients in the study. They identified eight patients suffering from PE: 30.8%. The GPs in the CG included 61 of their patients. Among them, four were suffering from PE: 6.6% (*p* value = 0.004, OR = 6.6768, 95% confidence interval (CI) (1.55; 34.40)).

